### Confidence in Saturated Fat Reductions

Various barriers could make it difficult to reduce your saturated fat intake. How certain are you that you could reduce it?

| I am confident I could reduce my saturated fat intake even if...                              |                 |                  |                  |                   |
|-----------------------------------------------------------------------------------------------|-----------------|------------------|------------------|-------------------|
|                                                                                               | Not at all
1 | Barely true
2 | Mostly true
3 | Exactly true
4 |
| I will have to make a detailed plan describing how to remember to buy low saturated fat foods |                 |                  |                  |                   |
| I have to rethink my behaviours and opinions concerning low saturated fat foods               |                 |                  |                  |                   |
| I will have to overcome my different high fat habits                                          |                 |                  |                  |                   |
| I will have to push myself                                                                    |                 |                  |                  |                   |

### Maintaining Saturated Fat Reductions

How certain are you that you could overcome difficulties when trying to maintain reductions in your saturated fat intake?

|                                                                                                                          |                 |                  |                  |                   |
|--------------------------------------------------------------------------------------------------------------------------|-----------------|------------------|------------------|-------------------|
| I am certain that I could overcome difficulties related to maintaining reductions in my saturated fat intake even if.... |                 |                  |                  |                   |
|                                                                                                                          | Not at all
1 | Barely true
2 | Mostly true
3 | Exactly true
4 |
| I am eating out                                                                                                          |                 |                  |                  |                   |
| High fat foods are more widely available than low fat foods                                                              |                 |                  |                  |                   |
| I am tired                                                                                                               |                 |                  |                  |                   |
| I am stressed out                                                                                                        |                 |                  |                  |                   |
| I feel tense                                                                                                             |                 |                  |                  |                   |
| I don't see success at once                                                                                              |                 |                  |                  |                   |
| My cholesterol does not improve immediately                                                                              |                 |                  |                  |                   |
| I won't get support for my first attempts                                                                                |                 |                  |                  |                   |
| It takes long to make it a habit                                                                                         |                 |                  |                  |                   |
| My partner/family/friends are not trying to reduce their saturated fat intake                                            |                 |                  |                  |                   |
| I cannot see any positive changes immediately                                                                            |                 |                  |                  |                   |

### Risk Perceptions

Please read the following statements and choose the one that best corresponds to you.

|                                                                                       |   |   |   |   |   |   |               |
|---------------------------------------------------------------------------------------|---|---|---|---|---|---|---------------|
| My chances of getting heart-disease in the short-term (e.g. next couple of years) are |   |   |   |   |   |   |               |
| Not at all strong                                                                     | 1 | 2 | 3 | 4 | 5 | 6 | 7 Very strong |

|                                                                                          |               |                        |         |                        |               |                         |
|------------------------------------------------------------------------------------------|---------------|------------------------|---------|------------------------|---------------|-------------------------|
| Compared to an average person of my age and sex, my chances of getting heart-disease are |               |                        |         |                        |               |                         |
| Much below average                                                                       | Below average | A little below average | Average | A little above average | Above Average | Much more above average |
| 1                                                                                        | 2             | 3                      | 4       | 5                      | 6             | 7                       |

### Saturated Fat Intake Plans

|                                        |            |             |             |              |
|----------------------------------------|------------|-------------|-------------|--------------|
| I now have my own plan regarding       |            |             |             |              |
|                                        | Not at all | Barely true | Mostly true | Exactly true |
| When to reduce my saturated fat intake |            |             |             |              |
| How to reduce my saturated fat intake  |            |             |             |              |

### Feedback on the Information Received

|                                                                                                  |                   |   |   |   |                |   |   |
|--------------------------------------------------------------------------------------------------|-------------------|---|---|---|----------------|---|---|
| I felt that the information provided by the study on heart-disease and saturated fat intake was: |                   |   |   |   |                |   |   |
|                                                                                                  | Strongly Disagree |   |   |   | Strongly Agree |   |   |
|                                                                                                  | 1                 | 2 | 3 | 4 | 5              | 6 | 7 |
| Trustworthy                                                                                      |                   |   |   |   |                |   |   |
| Of personal relevance to me                                                                      |                   |   |   |   |                |   |   |
| Enjoyable                                                                                        |                   |   |   |   |                |   |   |
| Interesting                                                                                      |                   |   |   |   |                |   |   |
| Contained a lot of new information                                                               |                   |   |   |   |                |   |   |
| Credible                                                                                         |                   |   |   |   |                |   |   |
| Worrying                                                                                         |                   |   |   |   |                |   |   |
| A wake up call                                                                                   |                   |   |   |   |                |   |   |

## **APPENDIX 5- Instructions on Planning**

### **Planning**

We would like you to plan how to reduce your saturated fat intake over the next two weeks. Below is a list of situations, e.g. I'm in the shops, and a list of different behaviours, e.g. I will choose margarine. Identify **as many situations** in which you would like to change your saturated fat intake and then try to match it with behaviours from the list below.

**Choose behaviours that you would like to change rather than ones that you are already doing.** By choosing a situation in which you are tempted to eat high saturated fat foods and then ways to overcome the temptation you are more likely to successfully reduce your saturated fat intake!

For example, you might find it useful to plan to put margarine on your bread instead of butter at lunch time. Then the situation-behaviour statement will become

e.g.

**If** I am .....having lunch.....**Then** I will.....choose Margarine (on bread).

| Situations                                   |  | Behaviours                                                |
|-----------------------------------------------------|--|------------------------------------------------------------------|
| If.....                                      |  | Then.....                                                 |
| I'm in the shop                                     |  | I will choose a lower fat dairy product or spread                |
| I'm having lunch                                    |  | I will go for fruit                                              |
| I'm getting a snack                                 |  | I will go for vegetables or salad                                |
| I'm having dinner                                   |  | I will check it's 5g or less in saturated fat per 100g           |
| I'm having breakfast                                |  | I will find out and choose the lower fat option                  |
| I'm in a restaurant                                 |  | I will go for grilled/steamed poultry or fish                    |
| I'm having a good time when
I'm out with friends |  | I will go for a short walk                                       |
| I am feeling depressed or down                      |  | I will call or find someone to talk to                           |
| I'm craving a high fat food                         |  | I will tell myself that if I try hard enough I can eat healthily |
| I'm feeling hungry                                  |  | I will distract myself with something else                       |
| I had a hard day                                    |  | I will reduce the amount of food I eat                           |
| Others around me are eating
high-fat foods       |  | I will not buy high fat foods to keep in the house               |
| I'm having a coffee/tea break                       |  | I will avoid others who are eating high fat foods                |

## **APPENDIX 6 – Recruitment Agency Screening**

### **Health Check Survey: Draft Questionnaire v2 2010 – Email Invite**

**Invite :**

From [name]  
Subject: Help us with our research

---

Dear panel member,

Today, we are inviting you to take part in a Health Check survey focusing on heart-health and healthy eating, which will involve carrying out a number of tasks. This will involve interacting with the system at three different times. The first time will not take more than 30 minutes. All those eligible and completing all three different interactions will be paid <<pointsAsMoney>> and their name will be also entered into a prize draw.

Instructions on how to take part can be found below. We look forward to hearing your opinions.

You can participate with this research project until <<end\_date>>. Please note this research project is limited to 900 respondents. Once 900 suitable respondents have completed the survey the project will be closed.

[name]  
SSI

# Health Check Survey: Draft Questionnaire v1 2010

## Page 1: Welcome

### Intro

Thank you for your interest in this survey. Please can you answer the following profiling questions by clicking on a box for each. This profiling survey is being conducted by an independent market research agency in accordance with the Market Research Society Code of Conduct. More info on survey?

[For more information about the survey please click here.](#)

### Age

[Ordered/Single]

Q1 What year were you born?

#### Answers

- Show as drop down list for the past 80 years (1927 to – last code – after 1991)
- List with most recent at the top

### SCREEN OUT IF BORN FROM 1991 ONWARDS

Create a hidden variable which means that age is grouped into the following bands for quotas/monitoring:

|                |   |       |
|----------------|---|-------|
| 29 or under    | 1 | CLOSE |
| 30 to 45 years | 2 |       |
| 46 to 60 years | 3 |       |
| 61 or over     | 4 | CLOSE |

### MaleFemale

[Ordered/Single]

Q2 Are you male or female?

#### Answers

|        |   |
|--------|---|
| Male   | 1 |
| Female | 2 |

### Region

[Ordered/Single]

Q3 Where do you live?

#### Answers

|                        |    |       |
|------------------------|----|-------|
| London/South East      | 1  |       |
| South West             | 2  |       |
| Eastern                | 3  |       |
| Midlands               | 4  |       |
| Wales                  | 5  |       |
| Yorkshire & The Humber | 6  |       |
| North West             | 7  |       |
| North East             | 8  |       |
| Scotland               | 9  |       |
| Northern Ireland       | 10 |       |
| Outside UK             | 11 | CLOSE |

### Survey Notes

[Info]

#### Important notes:

1. This is a genuine market research survey and not selling you anything

2. We make privacy a top priority - read our policy at <http://www.virtualsurveys.com/privacy/>
3. Whilst completing this survey your normal Internet connection charges will apply
4. With this survey, your computer has been sent a small piece of information (a cookie) to help us administer the survey. We also collect system data which will not be attributed to you personally
5. If you have any queries about these notes, or the survey, please email [[contact]](mailto:[contact]) or ring [name]
6. If you do not wish to complete this survey, simply close this window
7. Virtual Surveys is a UK based company and complies with UK and EU Data Protection Laws, but you should be aware that the Internet is an international medium and this may result in your data being processed outside the EU, you should only proceed with this survey if you consent to this

## Page 2: About You

### PersonalInfo

[Info]

Note this information will be used for analysis purposes only and will not be attributed to you personally

### Height

[Ordered/Multi]

Q4 How tall are you?

Answers

|             |    |      |
|-------------|----|------|
| Centimetres | 1  | OPEN |
| Feet        | 2  | OPEN |
| Inches      | 3  | OPEN |
| Don't Know  | 99 | Excl |

### Weight

[Ordered/Multi]

Q5 How much do you weigh?

Answers

|            |    |       |
|------------|----|-------|
| Killograms | 1  | OPEN  |
| Stones     | 2  | OPEN  |
| Pounds     | 3  | OPEN  |
| Don't Know | 99 | Excl. |

Q6 **BMI (HIDDEN QUESTION)**

[Ordered/Single]

Answers

|       |    |      |
|-------|----|------|
| 29.9  | 6  | Excl |
| 30    | 7  |      |
| 31    | 8  |      |
| 32    | 9  |      |
| 33    | 10 |      |
| 34    | 11 |      |
| 35    | 12 |      |
| 36-40 | 13 |      |
| 40+   | 14 |      |

### Smoker

[Ordered/Multi]

Q7 Which of these phrases best describes your smoking habits?

Answers

|            |   |
|------------|---|
| Smoker     | 1 |
| Non smoker | 3 |

### Heart

[Random/Ordered/Single]

Q8 Which, if any, of the following health problems have you ever been diagnosed with?

Answers

|                                                                         |   |       |
|-------------------------------------------------------------------------|---|-------|
| Diabetes                                                                | 1 |       |
| Heart disease                                                           | 2 | CLOSE |
| High blood pressure                                                     | 3 |       |
| Cancer                                                                  | 4 | CLOSE |
| Any other chronic disease of the major organs (e.g kidney failure etc.) | 5 | CLOSE |

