##### **Exclusion Criteria:**

- BMI <29 (Body Mass Index)
- <30 years old
- >60 years old
- Pregnant women
- Diagnosed with cancer
- Diagnosed with a heart-condition (heart-attack or angina) – this is because algorithms predict risk of first CVD event, not recurrent events.
- Any other chronic disease of the major organs (e.g. kidney failure)
- Not willing to sign online consent form
- Not literate in use of computer and the internet
- Not being able to print at home or at work

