### Phase 1 – Recruitment and Screening

Recruitment will be conducted by Virtual Surveys (<http://www.virtualsurveys.com/s>), an online recruitment agency, to cost effectively reach a specific target sample within the UK population. Virtual Surveys have their own online panel and a structured script will be used to screen individuals and exclude any people who do not meet the inclusion criteria (Appendix 6). Once subjects meet the inclusion criteria, they will be acquainted with the study procedures and asked to read an online informed consent form. They will be requested to click on a number of check boxes to make sure they have read and understood the information before they proceed to the online questionnaires. Participants will out items on their perceived saturated fat intake and social-cognitive determinants.

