**SCREENED:**

- AGE: Under 30 and over 60 (Q1/1 or 4)
- IF BMI <30
- DIAGNOSED WITH HEART DISEASE, CANCER OR ANY OTHER CHRONIC DISEASE OF THE MAJOR ORGANS AT Q8 (CODE 2, 4 OR 5)
- OUT OF QUOTA

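### The Appendix 6 screening script does not match the Section 4.2 eligibility criteria on BMI, pregnancy and multiple diagnoses

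*Protocol*

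**What the plan says.** Section 5.1, Phase 1, gives the script its role: "a structured script will be used to screen individuals and exclude any people who do not meet the inclusion criteria (Appendix 6".

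**BMI.** The exclusion list in Section 4.2 has "BMI <29 (Body Mass Index"), and its inclusion list has the matching limit of 29 or more. In Appendix 6 the screen-out list rejects a BMI below 30, and the accepted codes of the hidden BMI question (Q6 of the script) start at 30.

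**Pregnancy.** Section 4.2 excludes "Pregnant women". The same section describes the online screener as covering weight and height, age, gender, cardiovascular disease and cancer. Script questions 1 to 10 cover age, sex, region, height, weight, BMI, smoking, diagnoses, income and employment.

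**Diagnoses.** Question 8 of the script asks "Which, if any, of the following health problems have you ever been diagnosed with" and is tagged "Random/Ordered/Single". It has five codes: diabetes (1), heart disease (2), high blood pressure (3), cancer (4) and other chronic disease of a major organ (5). The screen-out rule is "DIAGNOSED WITH HEART DISEASE, CANCER OR ANY OTHER CHRONIC DISEASE OF THE MAJOR ORGANS AT Q8 (CODE 2, 4 OR 5"). For heart conditions Section 4.2 gives the reason for exclusion: "this is because algorithms predict risk of first CVD event, not recurrent events".

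**The concern.** The study runs wholly online. Part III marks source document verification as not applicable and says that no medical tests are performed. Who enters therefore depends largely on what the script asks and how it is coded. Where the script is stricter than Section 4.2, eligible people are lost. Where it is looser, people whom the protocol means to keep out can enter.

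Two matters are at stake. One is subject protection: someone with heart disease could be given a Heart-Age score from an algorithm that the protocol says does not apply to them, and a pregnant woman could enter despite the exclusion. The other is description: the report would state the Section 4.2 criteria while the sample had been selected by different ones.

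**Working it through.** No figure in the protocol bears on this point, so there is none to reproduce. The check sets Section 4.2 beside Appendix 6, item by item.

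**1. BMI**

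| Source | Admits | Rejects |
|---|---|---|
| Section 4.2 | 29 and above | below 29 |
| Appendix 6, screen-out list | 30 and above | below 30 |
| Appendix 6, hidden BMI question | codes from 30 up | 29.9 marked 'Excl' |

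The 'Excl' mark could mean 'exclusive', as it appears to beside the don't-know answers for height and weight. The screen-out list settles the script's intent without it. The band from 29 to just under 30 is thus eligible in one place and rejected in the other. Its width in body weight, from weight = BMI × height²:

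- 1.60 m: 29 × 2.56 = 74.2 kg to 30 × 2.56 = 76.8 kg
- 1.70 m: 29 × 2.89 = 83.8 kg to 30 × 2.89 = 86.7 kg
- 1.80 m: 29 × 3.24 = 94.0 kg to 30 × 3.24 = 97.2 kg

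This is roughly 2.6 to 3.2 kg at these heights. The protocol gives no BMI distribution for the panel, so the share of applicants in the band is unknown.

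**2. Pregnancy**

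None of script questions 1 to 10 asks about it. The screen-out list covers age, BMI, the three excluding diagnoses and full quotas only. Appendix 1 lists health status among the screening items without naming pregnancy. Table 2 in Section 3.1 sets a target of 25 women aged 30 to 45 in each of four arms, so 4 × 25 = 100 of the 400 subjects are women in the younger age group. The protocol gives no pregnancy rate.

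**3. Question 8**

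Take someone with high blood pressure (code 3) and heart disease (code 2).

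| Coding | Recorded | Result |
|---|---|---|
| Single answer | 2 | closed |
| Single answer | 3 | passes |
| Multi-answer, close on any of 2, 4 or 5 | 2 and 3 | closed |

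There are two passing codes and three closing codes, so 2 × 3 = 6 pairs of diagnoses leave the result to whichever one the respondent picks. How often such pairs occur, and which diagnosis people would pick, is not given.

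The tag also disagrees with the question. The stem allows for several diagnoses or none, but only one answer may be recorded and there is no code for none. The tag itself names both random and fixed order. Question 7, whose two smoking answers exclude each other, is tagged "Ordered/Multi". The single and multi tags may have been swapped.

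**4. Is there a later check?**

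The Heart-Age questionnaire in Appendix 4 asks again about heart disease, heart attack and heart surgery. By Section 5.1, Phase 2, it is completed after allocation and only by subjects going through Heart-Age, which is two of the four arms. The protocol does not say what follows a 'Yes'.

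**The case against.** The strongest reply concerns question 8. Its tag contradicts itself, the neighbouring tag looks misplaced, and the appendix is headed as a draft under two version labels. The stem and the closing rule both fit a multi-answer intent, so this may be a clerical slip. That stands, and it is why the point is put conditionally: the gap opens if the question is programmed as tagged. The tag still needs correcting, because this is the script that the protocol cites.

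A reader might infer that someone with no diagnosis cannot get through question 8. The document does not support that: nothing says an answer is forced, and the stem allows for none. A 'None of these' code is still worth adding, because it separates a true none from a skipped question.

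A reader might also infer that every pregnant woman who meets the other criteria would be enrolled. That cannot be verified. Subjects also tick boxes on an online consent form, which is not in the text available here, and a pregnancy statement could sit there. Being able to print and computer literacy are criteria that the script does not ask about either, so it may not be the only check.

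On BMI, the reply is that the mismatch spans one unit and only tightens entry, and that Section 1.5 equates obesity with a BMI above 30. But Section 1.3 names overweight as well as obese people as the target, so the document does not settle which limit is meant.

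Finally, screening comes before allocation, so these faults do not in themselves bias the comparison between arms. That is correct.

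**Conclusion.** The point holds. Section 4.2 and Appendix 6 contradict each other on BMI. The pregnancy exclusion has no item in the script shown or in the Section 4.2 screening list. The question 8 tag, if followed, lets a person with both a passing and an excluding diagnosis through. The BMI conflict is the firmest part and needs no assumption. The pregnancy part is limited to the script and the protocol text, since the consent pages could not be read. The question 8 part assumes that the tag is programmed as written.

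The number wrongly admitted or rejected cannot be calculated: the protocol gives no BMI distribution, no rate of combined diagnoses and no pregnancy rate. Any fixed share of such people passing question 8 would be invented.

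A reader might infer bias between the arms. The document does not support that directly, because the faults act before allocation. One caution follows from the later heart-disease item: if its answers were used to remove subjects, removal could occur only in the two Heart-Age arms. The protocol states no such removal. For the same reason the item cannot be counted as a safeguard. The harm is to who is enrolled and to subject protection, and it should be corrected before launch.

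**What to change.** - **BMI.** Reconcile the limit and use the same one in Section 4.2, the hidden BMI question and the screen-out list. The sponsor must decide which was intended.
- **Pregnancy.** Add an item to the script that closes on yes and include it in the screen-out list and the Section 4.2 screening list; or state where else this exclusion is applied.
- **Question 8.** Make it multi-answer with an exclusive 'None of these' code, close if any of codes 2, 4 or 5 is chosen, and clear the conflicting order tags. Make question 7 single-answer.

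The cost is minor survey reprogramming (two recodes, one added question, one aligned threshold) and matching edits to Section 4.2. It has to be done before launch, because people wrongly turned away or admitted cannot be re-screened afterwards without disturbing the sample.
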